### Secondary Objectives

1. To analyze per-patient sensitivity, specificity, and receiver-operating characteristic curves.
2. To analyze per-stent accuracy, sensitivity and specificity, and receiver-operating characteristic curves. For this analysis a statistical adjustment for clustering of stents within patients will be conducted using nonparametric analysis of variance.
3. To analyze interobserver variability in detection of coronary artery in-stent restenoses using MSCT.
4. To compare diagnostic accuracy for stents in different locations (coronary vessels), of different size and length, and for stents made of different materials.
5. To analyze the influence of different scan (heart rate, heart rate variability) and patient characteristics (gender, age, diabetes, body mass index) on image quality and diagnostic accuracy of MSCT.
6. To compare procedural complications of MSCT and conventional coronary angiography. These complications will include.
  - death,
  - stroke, and
  - myocardial infarction and
  - moderate to severe groin hematoma, groin pain, infections, allergies, thromboses, and arteriovenous fistula or other complications (if prolonging the in-hospital stay significantly [by at least 24 hours]).

- 
7. To analyze the cost-effectiveness using the primary and secondary efficacy data, the QALY data, and cost data derived from the trial.
  8. To analyze patient preference and satisfaction with and comfort during the imaging tests as recently described (Schönenberger et al. PLoS ONE 2007).
  9. To compare the amount of contrast agent and radiation exposure and the room time required (excluding time for interventions) of both tests.
  10. In addition, noncoronary causes of symptoms (e.g. pulmonary embolism, aortic dissection, pericarditis, pleural effusion, pneumonia, or hiatal hernia) will be recorded to analyze whether the cross-sectional imaging capabilities of MSCT might lead to a higher detection rate of those important incidental findings.
  11. To analyze which image quality in MSCT coronary angiography is required to directly reliably triage patients with suspected coronary artery in-stent restenoses.
  12. To analyze the correlation and agreement between MSCT coronary angiography and conventional coronary angiography (using quantitative analysis) for estimation of the percent diameter stenosis.

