### **Scanning and Reconstruction**

The stationary prospectively triggered scan of the coronary arteries shall cover the range from approximately 1 cm above the left atrium to the base of the heart. In addition, a single axial slice will be acquired at the largest diameter of the heart, which served to define the reconstruction field-of view to be used for all subsequent reconstructions. The size of this field-of view will be in the range of 180 to 220 mm in order to achieve an in-plane pixel size of approximately  $0.4 \times 0.4 \text{ mm}^2$  at an image matrix of 512 by 512. The reconstruction field-of view will be set to cover the entire heart and the descending aorta and will be used for CT coronary angiography. All MSCT scans will be performed at 0.5 mm detector collimation. The reconstructed slice thickness will be allowed to be 0.5 mm while the reconstruction interval will be allowed to be between 0.4 and 0.5 mm. The reconstructed FOV (round) shall be set at a maximum of 220 mm and a minimum of 180 mm in size. At the time of the MSCT, the images of the lungs and mediastinum (at large FOV, at least 320 mm) with a maximum reconstructed slice thickness of 5 mm (recommendation: 3-5 mm) will be immediately reviewed at the site for non-cardiac findings according to the MSCT SOP. The Radiology investigators will report these non-cardiac findings to the patient's clinical physician and to the patient in a timely fashion to immediately direct further necessary management.

For CTP imaging patients will receive adenosine at a standard dose ( $140 \mu\text{g/kg/min}$ ) through an intravenous line in the antecubital fossa of the left arm at least 20 min after nitroglycerin for CTA. Stress CTP will be performed 4:30 min after initiation of the continuous adenosine infusion.

Following the MSCT study, the patient will be monitored per local standard for at least 2 days to identify procedural complications. At least one post-MSCT set of vital signs will be obtained. The IV line will then be removed after the patient has been felt to have been adequately monitored.

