**Serious Adverse Events**

Serious adverse events will be recorded and classified according to the following categories.

1. Fatal;
2. Is life threatening?
3. Results in persistent or significant disability or incapacity
4. Is a congenital anomaly or birth defect?
5. Requires inpatient hospitalization or prolongation of existing hospitalization with the following exceptions:
  - a. Preplanned (prior to study), unless hospitalization is prolonged
  - b. Ambulatory treatment units or <24 hour re-hospitalizations
  - c. Hospitalization for elective procedure
  - d. Emergency room visit.

The procedure of reporting of Serious Adverse Events following MSCT is as follows:

1. Report any serious adverse events to the coordinating investigator within 24 hours of knowledge of event.
2. Report any serious adverse event to the IRB according to the local IRB procedures.
3. Complete appropriate Event Form for any complication and/or serious adverse events.
4. Attach physician /nurse notes or summaries regarding the event of to the Event Form.
5. Report of a patient death must be accompanied by a brief statement of the pertinent details, the death record, death certificates, and autopsy report (if performed).

---

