## **12 Quality Control and Assurance**

### **Methods Against Bias**

Diagnostic accuracy trials are significantly influenced by selection and verification bias. To avoid these biases we will include a consecutive cohort of patients which will thus be representative of patients with suspected coronary artery in-stent restenoses. To avoid verification bias MSCT will always be performed prior to conventional coronary angiography. This way it will be avoided that patients with positive findings on invasive imaging and the clinically driven necessity to perform an MSCT will be included in the trial. Also all patients will undergo conventional angiography regardless of the result of MSCT coronary angiography.

A primary concern is data quality with regard to transcription of original data from the patients' records to the CRFs. Thus the accuracy of every 10th data set will be compared with the original patient's files.

The coordinating investigator will assure the timely collection of complete and accurate data. There are two major steps associated with ensuring that accurate and complete data will be collected: 1) all persons associated with data collection should be properly trained and familiarized with the tasks that they are to perform; and 2) performance of the required procedures should be monitored and large deviations from study norms investigated.

Charité staff will prepare monthly patient recruitment reports showing the number of patients recruited for that week and cumulatively. In addition, a comparison to recruitment goals will be included. These reports allow the study leadership to monitor the recruitment and follow-up efforts. It is important for the statistical precision of the study to recruit all of the patients suggested by the sample size calculations and to obtain as much follow-up data as possible. In addition to the recruitment reports, a quarterly performance report will include information on the number and percent of forms or data delinquent.

Written CRFs will be used to capture data electronically. The data entry system program provides for editing of data, which includes range checking, table look-up for value accuracy, and intra and inter-form logical consistency checks. If an error occurs, the system automatically notifies the user, and if the error cannot be corrected immediately, errors will be printed out in hard copy for resolution by the study data manager.

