### **Time Intervals between Procedures**

MSCT coronary angiography is to be performed within 14 days after inclusion of patients for safety reasons. In no instance this time period is allowed to be delayed. Conventional coronary angiography will be performed within 14 days after MSCT.

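### Secondary objective 6 compares complications of MSCT and conventional angiography, but the protocol's rules for observing and counting them are uneven between the two tests (minor)

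*Protocol*

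**What the plan says.** Objective 6 (section 4, Secondary Objectives) sets out "To compare procedural complications of MSCT and conventional coronary angiography". It names death, stroke and myocardial infarction, and then "moderate to severe groin hematoma, groin pain, infections, allergies, thromboses, and arteriovenous fistula or other complications". A condition is attached at the end of that list: "or other complications (if prolonging the in-hospital stay significantly [by at least 24 hours".

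The two tests are given to everyone in one order. Section 12, Methods Against Bias, states that "MSCT will always be performed prior to conventional coronary angiography" and that "all patients will undergo conventional angiography regardless of the result of MSCT coronary angiography". Section 13, Time Intervals between Procedures, adds "Conventional coronary angiography will be performed within 14 days after MSCT". The opening of section 7 gives the same upper limit, and neither place gives a lower one. Section 5, Study Design, anticipates an imaging period of under a week.

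On observation, section 7 (Scanning and Reconstruction) says that after the MSCT study "the patient will be monitored per local standard for at least 2 days to identify procedural complications". Section 6, Physical Examination, has a 2-day observation after procedures related to the study, while section 6, Screening, describes the angiography as clinically indicated. In section 9 the monitoring subsection is headed for MSCT, and the reporting steps open with "The procedure of reporting of Serious Adverse Events following MSCT is as follows". Section 9, Clinical Adverse Events, is general: it records every clinical event with seriousness, date, intensity, onset and stop times, and relationship to study drug, contrast or procedure.

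**The concern.** A comparison of complications needs the same search, over the same period, with the same counting rule for both tests. Three stated features work against this.

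- **Observation and reporting.** The explicit window and the reporting steps attach to the index test. Whether the comparator is covered depends on whether a clinically indicated angiography counts as a study-related procedure, which the protocol does not settle.
- **Counting.** Several events that objective 6 names belong to arterial access. Most of the harms that section 9 lists for MSCT and its medication fall into the residual category, with its condition on length of stay.
- **Separation.** Angiography on the day of MSCT or the next day is not ruled out, so the MSCT observation can run through the catheterisation.

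At stake is how far the result of objective 6 can be interpreted. Section 8 lists the comparison under secondary efficacy endpoints, and objective 7 draws on secondary efficacy data for cost-effectiveness, so unevenness could carry over there.

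**Working it through.** **Plan's own figure.** The protocol gives no figure for objective 6. Its sample size of 90 belongs to the primary accuracy hypothesis (75% against 87%, two-sided 0.05, power 80%). It reproduces: [1.960 × √(0.75 × 0.25) + 0.842 × √(0.87 × 0.13)]² / 0.12² = 88.9, so 89 against the stated 90. It has no bearing on this point except as the number of patients.

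**Step 1: which rules name which test.**

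| Element | MSCT | Conventional angiography |
|---|---|---|
| Complication window | At least 2 days (section 7) | Only if it is a study-related procedure (section 6, Physical Examination) |
| Monitoring subsection (section 9) | Named in the heading | Not named |
| Serious-event reporting steps | Named | Not named |
| Clinical adverse-event page | Covered (all events) | Covered (all events), but the relationship field does not name either test |
| Laboratory event form | MSCT contrast named | At most under other agents |

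**Step 2: how events enter objective 6.**

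- Death, stroke and myocardial infarction count without condition.
- Groin hematoma, groin pain and arteriovenous fistula are named and come from arterial access. MSCT contrast goes through an antecubital vein.
- Infections, allergies and thromboses are named and could follow either test.
- Renal impairment, bradyarrhythmia, heart block, bronchospasm and hypotension are listed in section 9 as risks of MSCT contrast or medication. They are not named in objective 6. They enter only as other complications, and so only with at least 24 hours of added stay.

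This takes the condition to govern the last category alone. If it governs the whole bullet, allergies are filtered as well. Angiography is already planned for every patient, so an MSCT reaction that resolves before it may add nothing to the stay. The protocol does not say whether patients remain in hospital between the tests, so the size of this effect cannot be computed.

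**Step 3: what can be separated by timing.**

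- Onset before catheterisation: not attributable to angiography.
- Access-site events: attributable to angiography.
- Death, stroke, infarction, allergy, thrombosis, infection or renal change after a closely following angiography: may not be separable. For renal change, the only creatinine given a time is the one before MSCT, and contrast is given for each of the two CT studies before any angiographic contrast.

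**Step 4: how many patients could overlap.** The protocol gives no distribution of the gap, so this is an assumption. For a gap uniform on 0 to G days and an observation of w days, the share with catheterisation inside the observation is w/G.

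| Assumed gap | w = 2 days | w = 3 days (the text says at least 2) |
|---|---|---|
| 0 to 14 days | 2/14 = 14%, about 13 of 90 | 3/14 = 21%, about 19 of 90 |
| 0 to 7 days | 2/7 = 29%, about 26 of 90 | 3/7 = 43%, about 39 of 90 |

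Without the uniform assumption the possible range is 0% to 100%.

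**Step 5: direction.** The length-of-stay condition could hide MSCT harms, and a late MSCT event could be charged to the later angiography. Both would favour MSCT. Reporting steps written for MSCT could under-record angiography events, and an MSCT window running through the catheterisation could charge its events to MSCT. Both would count against MSCT. Nothing in the protocol allows these to be weighed.

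**The case against.** The strongest reply is that the protocol already collects much of what is needed. Section 9 records all clinical adverse events, with onset time and a relationship judgement, and all laboratory values are reviewed. The opening of the serious-event subsection is general, and since angiography always comes second, a serious event after it is also one that follows MSCT. Study-related procedures can be read to include an angiography that the protocol requires of everyone. The length-of-stay condition is the same for both tests, and an MSCT complication that delayed angiography could itself prolong the stay. The fixed order is a deliberate safeguard against verification bias. An attribution rule may properly sit in a statistical analysis plan, and the case report forms are not shown.

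Most of this stands. A reader might infer that delayed events cannot be assigned to either test at all; the onset times, the events before catheterisation and the access-site events show otherwise. A reader might also infer that only MSCT is monitored; the general adverse-event page contradicts that. The absence of an attribution rule would not by itself be a finding.

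Two things remain. The comparator's window and serious-event procedure depend on a favourable reading of ambiguous text, and the relationship field does not distinguish the tests. The counting rule, though identical in wording, bears unevenly on the two tests because of which events are named. An analysis plan cannot recover observations that were not made.

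**Conclusion.** The point holds as a minor one, confined to a single secondary objective. As written, objective 6 rests on uneven ascertainment and an uneven counting rule. In patients whose angiography follows closely, non-specific events after it may not be separable. Under a uniform gap and a 2-day observation this concerns 14% to 29% of patients (about 13 to 26 of 90). The uniform gap is an assumption, and the protocol allows anything from 0% to 100%. These figures count patients with overlapping observation, not misassigned events; the documents give no complication rate.

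It is tempting to conclude that the design makes MSCT look safer, or that the comparison cannot be interpreted. The documents support neither, because the possible biases run in both directions and part of the events can be assigned. The primary accuracy endpoint is not affected.

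**What to change.** Amend the wording of objective 6, section 6 (Physical Examination) and section 9, with the matching event form:

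1. Apply the same complication-observation window and the same event form to both tests, including the serious-event steps, and have the relationship field name MSCT or conventional angiography.
2. Count complications of both tests by the intensity and seriousness already recorded under Clinical Adverse Events, and report the count based on prolonged stay alongside.
3. Keep all patients in the comparison and report the actual gap between tests. Class non-specific events after an angiography that fell within the MSCT observation window as *not separable*, and give a sensitivity analysis that counts them against each test in turn.

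Restricting the main comparison to patients with a long gap is not advised: it would select on timing, which may follow clinical urgency, and would depart from the all-patients principle of section 5. The timing of angiography stays as it is. The cost is protocol and form wording, and slightly more event recording for angiography.

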## 5 Trial Design

### Number of Participants and Duration

90 adult men and women age 40 years or older with suspected coronary artery in-stent restenoses scheduled to undergo conventional coronary angiography will be included in this clinical trial and will be analyzed according to the intention-to-treat principle. The study will be conducted at the Charité and the enrollment period is expected to last about 8 to 12 months.

### Study Design

This is a prospective, comparative, intention-to-diagnose trial in patients with suspected coronary artery in-stent restenoses based on clinical or findings of other noninvasive tests according to the STARD statement. The current analysis will be performed in the intention-to-diagnose population without excluding patients or stents because of poor image quality. This study consists of three periods: Selection of Patients (see Chapter 6) and Imaging (see Chapter 7). For each patient, it is anticipated that the Selection period will last less than 1 day and will be followed by the Imaging period (less than 1 week).

### Withdrawal

Reasons for early withdrawal from a study may include but are not limited to:

1. Patient withdraws consent.
2. Any medical condition or situation that in the opinion of the investigator exposes the patient to significant risk by continuing the study.
3. Any serious adverse event, clinically significant event, or severe laboratory abnormality that may significantly increase the patient's risk in continuing in the study.

## 6 Selection of Patients

### Screening

Prospective patients with suspected coronary artery in-stent restenoses scheduled or planned to undergo further clinical evaluation with coronary angiography (within a maximum of 14 days) will be screened by personnel for possible inclusion into the study. The protocol inclusion and exclusion criteria will be reviewed for each potential participant. If the patient appears to be eligible for the study based on the initial evaluation, and will be undergoing clinically indicated coronary angiography, informed consent will be obtained. Baseline information and history will be collected after informed consent has been obtained using the appropriate CRFs (see Appendix 1). In addition, we will maintain an ongoing log for all patients who were screened for the study and reasons for not being enrolled. Consecutive patients with suspected restenoses will be included to ensure that the population studied is representative of the target population.

### Informed Consent

Written informed consent (using the consent form, CF, see CRFs Appendix 1) will be obtained from the patient. The consent process should be in accordance with local institutional standards. In general, the informed consent process involves an explanation of the purpose of the research study, a description of the procedures to be followed during the course of the study, the potential risks/benefits and the expected duration of the patient's participation. The patient should be provided a sufficient opportunity to review the CF and ask questions. Each patient will be assured that he/she is free to withdraw from the study at any time. The original informed consent must be kept on file by the investigator with the patient's record. A copy of the informed CF is to be given to each study patient.

Written Institutional Review Board (IRB) approval for the protocol and the informed CF will be obtained by the coordinating investigator. Any amendments to the protocol, as well as associated CF changes, must be submitted to the IRB, and written approval will be obtained prior to implementation.

### Inclusion Criteria

1. Suspected coronary artery in-stent restenoses based on clinical findings or findings on other noninvasive imaging tests and planned coronary angiography within the next 14 days. This clinical indication will be made by cardiologists. The activities of the cardiologists will be overseen and directed by the Cardiology Investigator of the Trial ([name]). All coronary artery stents (regardless of type and size) will be

---

eligible for inclusion in the trial. No maximum number of stents per patient will be used to exclude patients.

2. Able to understand and willing to sign the Informed CF.

## Exclusion Criteria

1. Creatinine of above 2.0 mg/dl
2. Age below 40 years
3. Women of child bearing potential (no hysterectomy, no menopause, or menopause since less than 12 months) must demonstrate a negative pregnancy test performed within 24 hours before MSCT or conventional coronary angiography.
4. Atrial fibrillation, uncontrolled tachycardia, A-V block II or III degree or other non-sinus rhythms
5. Body weight >300 kg (because of the weight limit of the CT)
6. Coronary artery bypass graft/s
7. Inability to hold the breath for 10 seconds
8. hypotension < 80 mmHg systolic
9. unstable angina pectoris, acute myocardial infarction < 48h
10. continuous therapy with dipyridamol (because of adenosine for CT perfusion)
11. AV-Block II oder III °

Patients with a known allergoid reaction to iodinated contrast agents in the past will not be excluded from the trial if they are considered to have a clinical indication for conventional coronary angiography but will be premedicated according to local standards using 250 mg of Solu-Decortin and 8 mg of Fenistil intravenously. An age limit of 40 years will be used as a balance between increased radiation exposure risks in younger patients and the necessity to include a representative spectrum of patients with suspected in-stent restenoses in the coronaries. Patients with a heart rate above 65 beats per min receive oral beta blockers because with beta blockers the heart rate can be reduced by an average of 10 beats and thus a maximum a heart rate of 60-70 beats per minute is expected during scanning which should give at least an adequate image quality using the most recent reconstruction approaches (17, 18). Patients with atrial fibrillation or uncontrolled tachyarrhythmia will also be excluded, because a regular heart beat is also essential for sufficient image quality with MSCT. Patients must be able to hold their breath for the duration of the MSCT scanning period (10 s). Because of the use of adenosine for perfusion, patients with systolic hypotension (<80 mmHg) and continuous therapy with dipyridamol cannot participate.

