## **Baseline Laboratory Tests**

Blood will be obtained either at the time of laboratory testing, MSCT (during IV placement) or at the time of cardiac catheterization, for cholesterol profile and serum biomarkers. A locally accepted/certified clinical pathology laboratory will perform the blood and urine tests specified by the protocol within 24 hours before CT. Serum chemistry profile will have to include BUN, creatinine, glucose, sodium, potassium, chloride and bicarbonate. If appropriate, a pregnancy test must also be performed. A qualifying serum creatinine must be performed immediately (maximum of 24 hours) before MSCT.

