### MSCT

All inclusion/exclusion criteria will be reviewed again just prior to the MSCT. Each participant will be clinically evaluated briefly before and following imaging.

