## **13 Ethics**

### **General**

The study will be conducted in accordance with the protocol, the current revision of the Declaration of Helsinki, the current guideline for Good Clinical Practice, and with the applicable regulatory requirements. The study protocol will have to be approved by the institutional review boards of each participating center. MSCT exposes the patients to a radiation dose of approximately 15 to 20 mSv. To ensure adherence to legal regulations and safety of the patients, the Federal Department for Radiation Protection will review the study protocol. Iodinated contrast agents will be used for MSCT. These agents have a well-known low risk profile (30). However, these agents will be administered twice for MSCT. Patients will benefit from the detection of noncoronary causes of their symptoms by MSCT.

Due to the importance of protecting study data at the Charité, access to all computer files and programs will be restricted to authorized personnel through the use of passwords and automatic access control at the file level. The Charité intranet has the latest firewall protection and the latest MacAfee virus protection, both of which are updated daily.

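### The pregnancy-test criterion names two alternative time windows, and the later one falls wholly after the study CT whenever angiography follows by more than 24 hours, which does not fit the protocol's other rules on testing and eligibility review

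*Protocol*

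**What the plan says.** Exclusion Criteria, item 3, defines women of childbearing potential and requires that they "must demonstrate a negative pregnancy test performed within 24 hours before MSCT or conventional coronary angiography". The two procedures are joined by a plain alternative.

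Four other places bear on when that test is due:

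- **Methods Against Bias** fixes the order: "To avoid verification bias MSCT will always be performed prior to conventional coronary angiography".
- **Time Intervals between Procedures** sets the gap: "Conventional coronary angiography will be performed within 14 days after MSCT". Study Design anticipates a shorter imaging period, under one week.
- **Baseline Laboratory Tests** says that a clinical laboratory "will perform the blood and urine tests specified by the protocol within 24 hours before CT", and later in the same paragraph: "If appropriate, a pregnancy test must also be performed".
- **Section 7, under MSCT**, adds: "All inclusion/exclusion criteria will be reviewed again just prior to the MSCT".

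**The concern.** A pregnancy criterion in an imaging study is there to keep pregnant women from being exposed by study procedures. Angiography is clinically indicated in these patients. The exposure that the study adds is the MSCT, with its radiation, two contrast injections and adenosine. A criterion whose wording can be met after that exposure does not do its work on that branch.

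Other eligibility checks are tied to a time before the scan. Creatinine is limited to the 24 hours before MSCT, and the ECG is due within 2 days before MSCT and is reviewed before inclusion. Item 3 differs in that its own text offers a later window. At stake is a clear rule for a small group of women, for whom an exposure cannot be undone. The accuracy estimate is not at stake.

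**Working it through.** The protocol gives no figure to reproduce. The check is day arithmetic on its stated windows, followed by a comparison of the texts.

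**Inputs.** MSCT comes first (Methods Against Bias). Angiography follows at a gap of *g* days, with *g* at most 14 (Time Intervals between Procedures) and anticipated below 7 (Study Design). The test window is 24 hours, or 1 day, before the named procedure (item 3).

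**Windows, with MSCT at day 0.**

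- MSCT branch: day −1 to day 0.
- Angiography branch: day *g* − 1 to day *g*.

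The angiography branch lies wholly after the scan when *g* − 1 > 0, that is, when *g* > 1 day.

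| Gap *g* | Angiography-branch window | Position relative to the CT |
|---|---|---|
| 1 day or less | starts at or before day 0 | can be met before the scan |
| 7 days (upper bound of the anticipated imaging period) | day 6 to 7 | wholly after |
| 14 days (outer limit) | day 13 to 14 | wholly after |

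For any gap above one day the two windows do not overlap, so the choice of branch decides whether the woman is tested before or after the CT.

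**Comparison with Baseline Laboratory Tests.** The general rule there points to the 24 hours before CT, which agrees with the MSCT branch and not with the angiography branch. The pregnancy sentence itself carries a condition and no time limit, whereas the creatinine sentence after it repeats its limit. The same section also lets blood for the cholesterol profile and biomarkers be drawn at catheterization, so not everything in it precedes the CT.

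**Comparison with the review before MSCT.** At that review, item 3 is either already met or not. If a negative result must be in hand, the angiography branch is unusable for any gap over one day and should not be in the criterion. If the branch is valid, the review cannot close item 3 before the scan. The two texts do not work together on either reading.

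**The case against.** The strongest reply is that the protocol should be read as a whole. A woman who has not been tested has demonstrated nothing when the criteria are reviewed just before MSCT, and Screening also has the criteria reviewed for each candidate. A pregnancy test is a blood or urine test specified by the protocol, so the rule of 24 hours before CT naturally covers it. The condition in "If appropriate, a pregnancy test must also be performed" is naturally read as meaning the women whom item 3 defines. A test in the 24 hours before CT satisfies every one of these places, so a site that follows the whole document would test before scanning.

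Most of this stands. A reader might infer from item 3 that the protocol lets untested women be scanned and that the safeguard fails completely. The documents do not support that, because the laboratory rule and the review before MSCT both work against it. What remains is that the timing of a safety test has to be inferred across sections, while the formal eligibility list carries the looser wording.

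Two further inferences should also be avoided:

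- The protocol states that "MSCT exposes the patients to a radiation dose of approximately 15 to 20 mSv". That is a dose to the patient. The protocol gives no fetal dose, and the figure should not be used as one.
- Read with strict literalism, a requirement placed in a list of exclusions would exclude women who test negative. The verb in item 3 makes the intent plain, so this is drafting style only.

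**Conclusion.** The point holds as an inconsistency. The angiography branch of item 3 can be met only after the study CT whenever the gap exceeds 24 hours, at the latest on day 13 to 14. That branch does not fit Baseline Laboratory Tests or the review of criteria before MSCT.

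The conclusion rests on reading the alternative in item 3 as written and on the stated order and maximum gap. It does not assume that any site would test late.

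The size is small. It concerns women aged 40 or over who have had no hysterectomy and are not yet 12 months past menopause. The protocol gives no count of them. The hypothesis, sample size, power and primary analysis are unaffected. It is still worth correcting, because it concerns patient safety and the correction is simple.

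**What to change.** Reconcile Exclusion Criteria item 3, Baseline Laboratory Tests and the eligibility review in section 7, so that the protocol states one unambiguous timing of the pregnancy test relative to MSCT and to angiography, in the same terms in all three places. The text should make clear whether the two procedures in item 3 are alternatives or each call for a test, and whether a result must be available at the review before MSCT. It should also tie the condition in Baseline Laboratory Tests to the group defined in item 3. Which clinical rule applies is for the sponsor to decide.

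In the same edit, word item 3 as an exclusion, so that it matches the list it stands in.

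The cost is about one sentence of amended criterion text with matching wording in the other two places, submitted to the review board as the protocol requires for any modification. The test is already planned, and the statistical design does not change.
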